# Research on allergic rhinitis improvement in asthmatic children after dust mite exposure reduction: a randomized, double-blind, cross-placebo study protocol

**DOI:** 10.1186/s13063-020-04614-6

**Published:** 2020-07-29

**Keywords:** Allergic rhinitis, Asthma, Dust mite

## Abstract

**Background:**

Allergic rhinitis (AR) in children is a major respiratory inflammatory disease with a high incidence that is increasing yearly. In China, 54.93% of children with asthma have AR, which often requires synchronous treatment. House dust mites (HDMs) are common allergens that often cause attacks of AR and asthma. Reducing allergen exposure is one of the most important measures to control and treat AR and asthma attacks. Hestelia Mite Bait, containing 0.1% emamectin, is a new tool for trapping and killing dust mites, reducing the number of dust mites on mattresses and thereby potentially reducing stimulation by allergens and ultimately improving asthma and rhinitis symptoms. This single-centre, randomized, double-blind, cross-placebo trial will explore the improvement in AR in asthmatic children after dust mite exposure reduction.

**Methods:**

We will recruit 60 children (aged 3–12 years) who have been diagnosed with AR and asthma and are allergic to dust mites as confirmed by a serum allergen test. Participants will randomly receive the Hestelia Mite Bait intervention for 8 weeks and the placebo intervention for 8 weeks. There will be a 4-week washout period between the two interventions. The primary outcome is the visual analogue scale (VAS) score of AR symptoms; the secondary outcomes include the Rhinitis Control Assessment Test (RCAT) score, Rhinoconjunctivitis Quality of Life Questionnaire (RQLQ) score, changes in the dust mite level, drug usage for asthma and AR, Asthma Control Questionnaire-5 (ACQ-5) score, and frequencies of acute asthma attacks, emergency visits, and hospitalizations.

**Discussion:**

This study aims to scientifically and objectively evaluate the effects of mite bait on rhinitis and asthma improvement after dust mite exposure reduction and provides a convenient means for future prevention and treatment of allergic diseases involving the airways in children.

**Trial registration:**

www.chictr.org.cn ChiCTR1900024688. Registered on July 21, 2019

## Introduction

### Background and rationale

Allergic rhinitis (AR) is a non-infectious disease of the nasal mucosa mediated by immunoglobulin E (IgE) after exposure to allergens. AR is a common allergic disease in children. The incidence of AR has increased to 10–30% in adults and to 40% in children [1]. AR manifests as sneezing, rhinorrhoea, sinus itch, and other symptoms, which have an adverse effect on quality of life, leading to disordered sleep breathing and increased incidence of attention deficit disorder [2, 3].

AR often coexists with organ-complicated allergic diseases, among which asthma is one of the most common conditions. In a Chinese epidemiological study, the incidence of asthma in children with AR was 35.01%, and the prevalence of AR in children with asthma was 54.93% [4]. AR and asthma have common pathophysiological elements. The immunopathologies of AR and asthma are similar in the cellular influx of eosinophils, mast cells, and T helper type 2 (Th2) cells. A similar array of mediators can be found in the lavage fluid of patients with AR and asthma [5]. Therefore, AR and asthma are proposed as “the same respiratory tract, the same disease”. In the presence of asthma, treatment of AR is often overlooked, and poor control of AR has been shown to be one of the causes of refractory and recurrent asthma [6–8]. Control of AR reduces the incidence of asthma attacks and associated hospitalizations [9].

Dust mites are a common trigger for AR [10]. The prevalence of house dust mites (HDMs) in AR patients in southern China is 95% [11]. Avoiding allergen exposure is an important measure to treat AR. Currently, reduced HDM exposure measures include keeping room humidity below 50%, wrapping mattresses and pillows with impervious covers, regularly cleaning bedding with hot water, removing carpets and plush toys, and regularly using high-efficiency particulate air filters and acaricides. A systematic review of randomized controlled trials was conducted in which HDM control measures were evaluated compared to placebo or other HDM avoidance measures in patients with clinically proven AR. In this review, seven of the nine trials reported that the interventions studied resulted in significant reductions in HDM load compared with the control. However, of the interventions studied to date, acaricides appear to be the most promising [12]. Hestelia Mite Bait, containing 0.1% emamectin, attracts dust mites into a mite trapping bag through the combined action of an oligomeric aromatic factor and dust mite atopic agents; then, it kills the dust mites, thereby achieving the goal of reducing allergens. Whether this new, safe, and effective tool to trap and kill dust mites can improve rhinitis and asthma symptoms has not been verified.

### Objectives

The purpose of this study is to evaluate the improvement in rhinitis and asthma symptoms after reduction of dust mite exposure with the acaricide Hestelia Mite Bait through a randomized, double-blind, cross-placebo clinical trial.

### Trial design

This is a randomized, double-blind, cross-placebo clinical trial to determine the improvement in rhinitis and asthma symptoms after dust mite exposure reduction. Participants will be randomly divided into 2 groups (group 1 and group 2). From the first day to the 8th week, the patients will apply mite baits or the placebo packages and complete questionnaires three times (V1–V3, V1 = the first day after enrolment; V2 = the fourth week plus or minus 3 days after enrolment; V3 = the eighth week plus or minus 3 days after enrolment). House sampling will be conducted twice (V1 and V3) during this period. After 4 weeks of washout, day 85 marks the beginning of the second phase of treatment.

During this period, the patients will be crossed to accept different interventions for 8 weeks. Questionnaires will be completed three times again (V4–V6, V4 = the twelfth week plus or minus 3 days after enrolment, V5 = the sixteenth week plus or minus 3 days after enrolment, V6 = the twentieth week plus or minus 3 days after enrolment), and house sampling (V4 and V6) will be completed twice again. Finally, we will conduct the questionnaire survey 4 weeks after the end of the intervention (V7, V7 = the twenty-fourth week plus or minus 3 days after enrolment). Throughout the study, the children will receive standard treatments in accordance with asthma and AR guidelines [13]. The efficacy of mite bait in reducing AR and asthma symptoms will be assessed using a visual analogue score (VAS) for rhinitis symptoms, Rhinitis Control Assessment Test (RCAT) score, Rhinoconjunctivitis Quality of Life Questionnaire (RQLQ) score, changes in the level of dust mites, drug usage for asthma and AR, Asthma Control Questionnaire-5 (ACQ-5), and frequencies of acute asthma attacks, emergency visits, and hospitalizations.

## Methods: participants, interventions, and outcomes

### Study setting

The target population for this trial will be recruited from the respiratory clinic of Shanghai Children’s Medical Center, a tertiary first-class paediatric hospital with a large number of outpatients with asthma and rhinitis and a professional respiratory medical team.

### Eligibility criteria

#### Participants

Inclusion criteria
Aged 3–12 years, male or female.Children diagnosed with AR in accordance with the 2019 guidelines for diagnosis and treatment of AR [13]. At the same time, the diagnosis must conform to the diagnostic criteria for childhood asthma formulated by the National Children’s Asthma Prevention and Treatment Cooperation Group in 2016 [﻿14﻿].Maintained use of guide-based rhinitis and asthma control drugs for the previous 1 month. Inhaled drugs, such as budesonide suspension, fluticasone aerosol, salmeterol dry powder inhalation, and budesonide formoterol dry powder inhalation, could be used to control the condition according to age characteristics.Performance of the serum-specific allergen test, with the level of dust mite allergen sIgE > 0.35 IU/mL considered positive.Written informed consent provided by the guardians of all subjects (approved by the Ethics Committee of Shanghai Children’s Medical Center affiliated with Shanghai Jiao Tong University School of Medicine).Agreement to collect dust mites from indoor mattresses.

Exclusion criteria
Basic diseases, such as congenital heart disease, immune deficiency, gastroesophageal reflux, bronchopulmonary dysplasia, and obliterative bronchiolitis.Inability to sleep in a separate bed.Participation in other clinical studies within the past 3 months.

### Process of obtaining informed consent

[name], a staff member hired by the trial sponsor, will post recruitment information on the WeChat official account “Respiratory Angel” of the Department of Respiratory Medicine of the Shanghai Children’s Medical Center and collect the information of participants through Wenjuanxin, a platform providing functions equivalent to Amazon Mechanical Turk. Finally, [name] will contact the guardians of qualified patients through WeChat and receive written informed consent.

### Additional consent provisions for collection and use of participant data and biological specimens

On the consent form, participants will be asked if they agree to the use of their data should they choose to withdraw from the trial. Participants will also be asked for permission for the research team to share relevant data with people from the universities participating in the research or from regulatory authorities, when relevant. This trial does not involve the collection of biological specimens for storage. The form used to obtain informed consent is available from the corresponding author on request.

## Interventions

### Explanation for the choice of comparators

We will compare Hestelia Mite Bait containing 0.1% emamectin with a placebo that has a consistent appearance and odour but no acaricidal effect to investigate the change in dust mite exposure and the improvement in asthma and rhinitis symptoms after indoor use of the mite bait.

### Intervention description

After recruitment (V0), baseline medical characteristics (name, age, sex, diagnosis of asthma and rhinitis and the allergen test report) will be collected. The subjects will be randomly divided into 2 groups. The children randomly assigned to group 1 will be placed with package A for an 8-week intervention. All HDM species reach adulthood within 3 to 4 weeks. Once mature, adult mites have a life expectancy of between 4 and 6 weeks [15]. To avoid an impact of the first intervention on the subsequent intervention, we will establish a 4-week washout period according to the growth cycle of the dust mites. After the 4-week washout period, package B will be placed for an 8-week intervention. In group 2, package B will be placed for an 8-week intervention, followed by a 4-week washout period and then package A will be placed for an 8-week intervention. Each child will undergo a total intervention period of 16 weeks, a washout period of 4 weeks, and a follow-up period of 4 weeks after the end of the second intervention. A flow chart of the study is shown in Fig. 1. At V1, V3, V4, and V6, the staff will collect indoor samples from mattresses using a glass fibre membrane, mite-clearing vacuum cleaner. The components of dust mite antigens in the collected samples will be detected via enzyme-linked immunosorbent assays. Parents will be asked to evaluate the AR and asthma symptom scores and clinical event records at V1–V7 (see the outcome indicators for details), as shown in Table 1.

**Fig. 1 Fig1:**
[figure not shown]
Study flow chart

**Table 1 Tab1:**
[figure not shown]
Study schedule

*Bag A and bag B are indistinguishable from each other in terms of packaging and smell, and whether they contain placebo or mite bait will be known only to the pharmacist

### Criteria for discontinuing or modifying allocated interventions

If the research physician feels that it is not in the child’s best interest to continue participating in the study (e.g. if there is an allergic reaction to the mite bait or placebo used), he/she may decide whether to withdraw the child from the study at any time. If a subject’s parents fail to complete the questionnaire after 3 reminders or fail to cooperate with the indoor sample collections, the subject will be considered poorly compliant and will be excluded from the study.

### Strategies to improve adherence to interventions

First, we will explain our study to each child’s parents as follows: the enrolled children will receive regular follow-up, a questionnaire evaluation, and standardized treatment by respiratory specialists at Shanghai Children’s Medical Center. The detection of the HDM antigen concentration in the bedroom mattress is free of charge, and the mite bait and placebo package are safe. This is the only hygienic product for dust mite removal certified by the Ministry of Agriculture in China and has a product registration certificate (registration certificate number: WP20180004). During the study, professional staff will enter the room four times to clean the mattress using a mite-removing vacuum cleaner and collect the attractors. The entire process requires the cooperation of family members, and parents need to complete the questionnaires within 10–20 min.

Second, during the implementation process, we will regularly remind parents to fill out the questionnaire via WeChat. The research team will provide help and detailed answers to parents’ questions during the trial.

### Relevant concomitant care permitted or prohibited during the trial

The original asthma medication can be maintained during the trial. When acute asthma attack symptoms occur, β2 agonists will be used to relieve bronchospasm, and depending on the clinical severity, oral or intravenous corticosteroids will be used until the symptoms are relieved. However, during the test, the children will not be allowed to go outside for long periods of time and must remain indoors in a room with mite bait or placebo at night when they sleep.

### Provisions for post-trial care

Patients with adverse reactions that occur in the context of the study will be followed up by the investigator and receive help from our professional medical team until the problem is resolved. After the entire test, each family will get the bait mite for free.

### Outcomes

#### Primary outcome

VAS for clinical symptoms of AR○ In 1988, Linder first applied the VAS to assessment of AR symptoms, demonstrating its sensitivity and specificity [16]. Patients will be scored using the VAS for symptoms occurring during the previous week, including sneezing, rhinorrhoea, nasal itching, nasal congestion, itchy eyes, teary eyes, foreign body sensation, and red eyes, for a total of eight symptoms. The VAS is a 10-cm line bounded on one end with a score of 0 and on the other end with a score of 10 that is used to show the severity of a patient’s symptoms (“0” for no symptoms and “10” representing the most severe symptoms). Patients will be directed to mark the symptom scores on the scale according to their perception of their symptoms.

#### Secondary outcomes

Change in the RCAT score○ The RCAT demonstrated adequate reliability, validity, and responsiveness and was deemed acceptable and appropriate by the patients. This tool can facilitate detection of AR symptom-control problems, and its brevity supports its usefulness in clinical care. The RCAT consists of 6 items: nasal congestion, sneezing, watery eyes, sleep problems caused by rhinitis, activity avoidance, and rhinitis symptom control. Responses are measured on a 5-point Likert-type scale. RCAT scores range from 6 to 30, with higher scores indicating better rhinitis control [﻿17﻿].Change in the ACQ-5 score○ The ACQ-5 is a questionnaire composed of 5 simple multiple-choice questions that are scored on a scale. The results are obtained by adding the total points and averaging them. It is a rapid assessment tool and plays a significant role in evaluating the extent to which asthma is controlled. Each child will be asked to evaluate the level of asthma control in the previous week. The lower the score is, the better the control level.RQLQ for children with AR [﻿18﻿]○ In this study, children with rhinitis during the previous 1–2 weeks will be evaluated on the basis of their symptoms, psychological status, mental status, social communication, and other aspects of 14 problems caused by rhinitis. The questionnaire is based on a scale according to the following point values: 0 points, normal; 1 point, slight; 2 points, mild; 3 points, serious; and 4 points, very serious. The higher the score is, the more severe the effect of rhinitis on the quality of life.Changes in levels of dust mite antigen in children’s beds○ Three sampling points will be randomly selected for each mattress, and each sampling point will have a range of 30 cm^2^. Each sampling point will be repeatedly vacuumed 10 times using a glass fibre membrane, mite-clearing vacuum cleaner (the bed area will be recorded at the same time). Dust on the glass fibre membrane in the vacuum cleaner will be put into a plastic bag and stored at − 20 °C (killing the dust mites). The samples from each family will be weighed, and then, allergens will be extracted. ELISAs (Indoor Biotechnologies, Charlottesville, VA, USA) will be used to detect the dust mite antigens Der p2 (*Dermatophagoides pteronyssinus*) and Der f2 (*D. farinae*) in the extracted solution.Use of medicines for AR and asthma in children○ The percentages of the children who frequently used anti-asthma drugs for control of rhinitis during the previous 4 weeks were as follows: no use ever, 0%; a total of 1 week of use, 25%; and use every day, 100%. Specific drugs include physiological saline, nasal spray hormone (Mometasone Furoate Aqueous Nasal Spray, Fluticasone Propionate Nasal Spray, Budesonide Nasal Spray, etc.), oral allergy drugs (cetirizine, loratadine, levocetirizine, desloratadine, etc.), Sinupret Drops, montelukast, traditional Chinese medicine (Tongqiao Biyan Granule, Biyuanshu Oral Liquid, Xinqin Granule), nasal allergy medications (levocabastine, azelastine hydrochloride), desensitization treatment (Dermatophagoides Farinae Drops), and inhaled hormones to control asthma (Budesonide Suspension For Inhalation, Seretide, Flixonase, Symbicort Turbuhaler).Number of asthma attacks, emergency visits, frequency of hospitalization

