## Statistical methods

### Statistical methods for primary and secondary outcomes

SPSS 20.0 software will be used to analyse the experimental data. Descriptive statistics will be used for the following data analyses: categorical variables, namely, RCAT scores, ACQ-5 scores, drug usage for asthma and AR, and frequencies of acute asthma attacks, emergency visits, and hospitalizations via frequency tables (i.e. number of evaluable subjects, frequency and percentage for categorical values). The mean ± SD, median, minimum, and maximum will be used as continuous variables, namely, the VAS scores and RQLQ scores. One-way analysis of variance and a two-sample *t* test will be adopted for normally distributed data, and a non-parametric rank-sum test will be adopted for non-normally distributed data. Fisher’s exact and chi-square tests will be used to compare classified data, and *P* < 0.05 will be considered statistically significant.

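### The drug-use outcome is labelled a percentage of children but scored as one child's share of 28 days, with three scores given and a categorical analysis planned

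*Protocol article*

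**What the plan says.** Under Secondary outcomes, the item on use of medicines for AR and asthma opens with a group quantity: "The percentages of the children who frequently used anti-asthma drugs for control of rhinitis". The recall window and the values that follow, which are set by how long the drug was used, read: "during the previous 4 weeks were as follows: no use ever, 0%; a total of 1 week of use, 25%; and use every day, 100" (per cent). No other duration is given a value, and nothing says that values in between are interpolated.

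The drug list begins "Specific drugs include physiological saline, nasal spray hormone" and goes on through oral antihistamines, montelukast, traditional Chinese medicine, desensitization treatment and inhaled steroids for asthma.

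The section on statistical methods for primary and secondary outcomes summarises as "categorical variables, namely, RCAT scores, ACQ-5 scores, drug usage for asthma and AR", together with the event frequencies, by frequency tables showing "number of evaluable subjects, frequency and percentage for categorical values". Only the VAS and RQLQ scores are named as continuous. Fisher's exact and chi-square tests are planned for classified data.

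**The concern.** The item names one quantity and scores another. A percentage of children belongs to a group; a value fixed by whether a drug was used for no days, one week or every day belongs to one child. The group proportion cannot be computed from the text either, because frequent use is not tied to any of the three values.

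The range without a score matters for this population. The eligibility criteria require rhinitis and asthma control drugs to have been maintained for the previous month, and standard treatment continues throughout. If the bait reduces the need for drugs, a plausible pattern is a partial cut from frequent use, between one week and every day. The text gives no score there. The drug-use result could then depend on how parents or analysts filled the gap rather than on what the children used.

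**Working it through.** **Inputs.** From Secondary outcomes: a recall window of 4 weeks, that is 28 days, and three values (no use 0%, one week in total 25%, every day 100%). From the statistical methods: drug usage is categorical.

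**Step 1: reproduce the stated values.** Share of time for one child = days used / 28 × 100.
- 0/28 × 100 = 0%
- 7/28 × 100 = 25%
- 28/28 × 100 = 100%

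All three reproduce exactly, so the scale is a per-child share of time and not a percentage of children.

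**Step 2: count the durations without a score.** A child can have 0 to 28 days of use, which is 29 values. Three have a score. Those without are 1 to 6 days (6 values) and 8 to 27 days (20 values): 6 + 20 = 26 of 29. If the 25% value is read generously as covering anything up to a week, the 20 values from 8 to 27 days still have none.

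**Step 3: reading A, only three levels exist.** An intermediate answer must be moved to 0, 7 or 28 days, and the text gives no rule for this. I tried three rules, all of them assumptions: nearest level, round down, round up. The table shows the fall in percentage points.

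| Change in days | True fall (share of time) | Nearest | Down | Up |
|---|---|---|---|---|
| 28 to 14 | 100 − 50 = 50 | 75 | 75 | 0 |
| 28 to 21 | 100 − 75 = 25 | 0 | 75 | 0 |
| 27 to 18 | 96.4 − 64.3 = 32.1 | 0 | 0 | 0 |

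For the first row, 14 days is 7 days from the one-week level and 14 days from the daily level, so nearest and down both give 25%, a fall of 75; rounding up gives 100%, a fall of 0. For the third row, nearest and up send both 27 and 18 days to 100%, and down sends both to 25%, so every rule records no change.

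**Step 4: reading B, the three values are anchors of a 0 to 100% scale.** Then 14 days scores 50%, 18 days 64.3% and 27 days 96.4%, and the record itself loses nothing. Two faults remain. The group label is wrong, since the score belongs to one child. And a frequency table with a chi-square or Fisher's exact test treats the scores as unordered classes: it does not use the fact that 96.4% to 64.3% is a fall of 32.1 points.

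**The case against.** The strongest reply is that reading B is the more natural one. Three values lying exactly on days/28 look like worked examples, and a deliberate three-option item would hardly jump from one week to every day. The categorical list is also weak evidence for reading A, because it includes RCAT scores (6 to 30) and ACQ-5 scores (a mean of five items), neither of which has three levels. The questionnaire is not shown, and an article can leave response formats to it. All of this stands, and it makes the loss of information at recording conditional. It does not rescue the text: under reading B the unit is still misnamed and the planned analysis still ignores the scale.

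A reader might go further and infer that partial reductions in drug use are certainly lost, and lost for good because a submitted questionnaire cannot be changed. The documents do not support this. The rule under Data collection and management bars edits after submission; it does not say which answers were offered. Nor can an average distortion be given for the trial, since the protocol states neither a rounding rule nor any distribution of starting use.

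The mismatch between the phrase about anti-asthma drugs and the list is mostly a slip. The item's own heading covers both diseases, and the list fits that heading.

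**Conclusion.** The definition contradicts itself and needs correction on either reading. What is certain from the text: the label is a group percentage, the values are per-child shares of 28 days, 26 of 29 day counts have no score when read literally, and the analysis is categorical. What is conditional: if only three levels are recorded, the same change in use can read as 75 points or as nothing, and a fall of 32 points can disappear under all three rounding rules tried. Those figures are examples for single children, not estimates for the trial. If the values are anchors, the cost is a wrong unit and an analysis that discards the size of the change.

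This is a minor point. Medicine use is one of several secondary outcomes, and neither the VAS analysis nor the sample size depends on it.

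**What to change.** In Secondary outcomes, define the measure per child as the number of days used in the previous 28 days, divided by 28 and multiplied by 100, for the listed drugs, with rhinitis drugs and asthma drugs shown separately. Delete the wording about the percentage of children who frequently used them. In the statistical methods, move drug usage from the categorical to the continuous variables.

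The cost is a few sentences of text and, if the form does not already ask for days, one reworded question. No extra visits or participants are needed. The small downside is that parents must recall a number of days. A complete set of ordered categories covering 0 to 28 days, analysed as ordered, would also remove the contradiction, with less detail. If the form in use offered only three options, the report should say so and state how intermediate use was assigned.
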